### Study dropouts

Participation in the trial is voluntary, and patients will have the right to withdraw consent at any time, for any reason, without any consequence for further medical treatment. The reasons and circumstances for study discontinuation will be documented in the CRF. The patients’ participation in this study can also be ended by the investigator if the patient is uncooperative and/or does not attend the study visits. In this case, patient data collected up until the point of removal will be included in the analysis; if too many data are missing (e.g., missing baseline, study visits, and other measurements included in the primary outcome), the patient will be replaced by a new patient. Patients who convert to open surgery will be treated according to the standard of care, based on the findings during surgery. These patients will be excluded from the study, and patient data until this moment will be included in the analysis.

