### Study visits and data collection

Patients will be visited preoperatively, intraoperatively, daily between POD 1 and 3, and on discharge. Patients will be contacted by phone on PODs 30 and 90 (Fig. 2).

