#### Analysis

Continuous distribution of the data was assessed by visual inspection of histograms and D’Agostino–Pearson’s normality tests. For both arms, the baseline characteristics will be expressed as counts and percentages, means and standard deviations, or medians and interquartile ranges, as appropriate.

Ventilatory parameters and vital signs during the surgery will be analyzed using a mixed-effect model with repeated measures, and with patients as a random effect. No or minimal losses to follow-up for the primary and secondary outcomes are anticipated. The intention-to-treat (ITT, all randomly assigned cases) population is used for all outcomes analysis. The supportive analysis is based on a full analysis set (FAS, all randomly assigned patients who received corresponding PP until liver resection). However, if more than 1% of missing data are found for the primary outcome, a sensitivity analysis using multiple imputations and estimating equation methods will be carried out.

Hypothesis tests will be two-sided with a significance level of 5%, with the exception of the primary outcome.

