#### Secondary outcomes

Postoperative organ dysfunction and complications within 30 days will be classified according to the classification described by Dindo et al. [24] and defined as a dichotomous composite endpoint, while ICU admission and readmission will be given as a percentage. Scores for PQRS will be given as the mean and standard deviation per time point per treatment arm. The correlation between IVC-CI and CVP will be tested using the correlation analyses.

The effect of the intervention on secondary binary outcomes will be assessed using the risk ratio and 95% CI calculated with Wald’s likelihood ratio approximation test and *χ*^2^ tests for hypothesis testing. The effects of the intervention on hospital-free days at day 28 will be estimated with a Student’s *t* test and reported as the mean difference between the two groups. The consistency of the findings of the Student’s *t* test for the hospital-free days at day 28 will be confirmed according to the mean ratio, as calculated by a generalized additive model considering a zero-inflated beta distribution.

Finally, 90-day mortality will be assessed using Kaplan–Meier curves, and hazard ratios with 95% confidence intervals will be calculated using Cox proportional hazard models without adjustment for covariates. The proportional hazard assumptions will be tested using scaled Schoenfeld residuals, and alternative parametric survival models will be used if the proportionality assumption is not sustained.

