Complications related to gas embolism should be considered carefully, as gas embolism resulting from pneumoperitoneum establishment has been shown to be associated with a 28% mortality rate after laparoscopic cholecystectomy [32]. CO_2_ gas embolism in laparoscopic surgery may also cause postoperative cardiac arrest [2], cerebral infarction [3], and even death [33]. We reported a case of CO_2_ embolism during laparoscopic nephrectomy without evidence of right-to-left shunt, in which the patient suffered from slurred speech and developed epileptiform seizures 9 h after the surgery [34]. Once gas embolism occurs during LLR, it may affect cardiopulmonary function and even cause neurologic deficits, resulting in delayed postoperative recovery. In this study, TEE will be used for gas embolism monitoring because it is capable of detecting 0.02 mL/kg of gas. Cerebral oxygen will also be observed to prevent cerebral embolism caused by micro emboli. TEE has no effect on cerebral oxygen because the baseline values are mainly related to cardiac function [35].

The occurrence of CO_2_ embolism likely depends on several variables. Surgical duration and size of parenchymal transection are likely to be directly proportional to the risk of gas embolism [36]. Intraperitoneal pressure may also play a role. Indeed, a higher PP led to higher degrees of embolization after laparoscopic IVC injuries in anesthetized pigs [13]. Hence, low-PP surgery is attractive, especially in reducing the incidence of embolism and its related complications. In addition, clinically, the most important benefit of low-PP is lower postoperative pain scores, which accelerate postoperative recovery [12]. No previous studies have compared the incidence of gas thrombosis in low versus standard PP during elective LLR. Therefore, we hypothesized that a low PP (10 mmHg) with controlled-low-CVP will lead to less severe gas embolism and promote postoperative recovery as compared to standard PP (15 mmHg) in elective LLR. To better evaluate the prognosis, PQRS will be used to assess recovery after LLR according to six dimensions of health, including physiologic, nociceptive, emotive, activities of daily living, cognitive, and overall patient perspective [18].

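### Ending participation for non-cooperation or missed visits stops collection of the late secondary outcomes that the ITT analysis of all randomised patients needs

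*Protocol article*

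**What the plan says.** Study dropouts (protocol article) covers patients who withdraw consent and then adds a rule for the investigator: participation "can also be ended by the investigator if the patient is uncooperative and/or does not attend the study visits". For a patient removed in this way, "patient data collected up until the point of removal will be included in the analysis". If too much is missing, "the patient will be replaced by a new patient". Nothing in the article provides for contacting a removed patient again or for reading later outcomes from the hospital record.

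The Analysis section states: "The intention-to-treat (ITT, all randomly assigned cases) population is used for all outcomes analysis". It expects little or no loss to follow-up. It plans multiple imputation and estimating equations as a sensitivity analysis only if more than 1% of primary outcome data are missing.

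Several secondary outcomes mature after the inpatient visits. Study visits and data collection states: "Patients will be contacted by phone on PODs 30 and 90". Secondary outcomes states: "Postoperative organ dysfunction and complications within 30 days will be classified according to the classification", as a dichotomous composite, and "90-day mortality will be assessed using Kaplan–Meier curves", with a Cox model. Hospital-free days at day 28 and unexpected ICU admission or readmission are also listed under Outcomes.

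**The concern.** An ITT analysis of all randomised patients needs outcome data on all of them. This rule lets data collection stop for a reason other than withdrawn consent, although the remaining outcomes ask little of the patient. Discharge date and ICU use are in the record, and complications and survival need one or two calls that are already scheduled.

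The loss may also be related to outcome. The Discussion says that once gas embolism occurs, "it may affect cardiopulmonary function and even cause neurologic deficits, resulting in delayed postoperative recovery", and the PQRS is given verbally. A patient who is doing badly may therefore be less able or willing to complete assessments. If such patients are removed, the observed complication rate is too low, and censoring at removal in the Kaplan–Meier and Cox analyses may not be independent of the risk of death. The planned sensitivity analysis does not reach these outcomes, and no later analysis can recover data that were never collected.

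**Working it through.** **Step 1. Which outcomes are exposed.** This sets Outcomes, Quality of recovery, and Study visits and data collection against the removal rule.

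| Outcome | When collected | Effect of removal after surgery |
|---|---|---|
| Severe gas embolism (primary) | By TEE during the resection | Already complete and kept |
| Intraoperative complications, surgeon satisfaction | During surgery | Kept |
| PQRS | PACU, POD 1, POD 3 | Only time points after removal are lost |
| Hospital-free days at day 28, ICU admission or readmission | Hospital record | Events and dates after removal are lost |
| 30-day complications | Until discharge, then the POD 30 call | Events after removal are lost |
| 90-day survival | POD 30 and POD 90 calls | Censored at removal |

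The conflict with ITT is therefore confined to the late secondary outcomes.

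**Step 2. The plan's own loss allowance.** The stated sample size reproduces with the unpooled two-proportion formula: (0.69 × 0.31 + 0.45 × 0.55) × ((1.960 + 0.842)/0.24)² = 62.9, so 63 per arm and 126 in total. Then 126/(1 − 0.10) = 140. The allowance is 140 − 126 = 14 patients, or 7 of 70 per arm. The point does not depend on this calculation, which only supplies a scale for loss.

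**Step 3. What a given loss leaves undetermined.** The documents give no removal or complication rates. Assume a 20% 30-day risk among observed patients and k of 70 removed per arm. The lowest possible risk in an arm is 0.20 × (70 − k)/70. The highest is (0.20 × (70 − k) + k)/70. The extreme risk ratios set one arm at its lowest and the other at its highest.

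| k per arm | Range of risk in an arm | Range of risk ratio |
|---|---|---|
| 1 | 19.7% to 21.1% | 0.93 to 1.07 |
| 3 | 19.1% to 23.4% | 0.82 to 1.22 |
| 7 | 18.0% to 28.0% | 0.64 to 1.56 |

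For k = 7: 0.20 × 63 = 12.6; 12.6/70 = 0.18; 19.6/70 = 0.28; 0.18/0.28 = 0.64; 0.28/0.18 = 1.56.

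**Step 4. Direction of bias.** Observed risk = (true risk − share removed × risk among removed)/(1 − share removed). Every input below is assumed.

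- *True risks 20% (low PP) and 30% (standard PP); 5% and 15% removed; 60% of removed patients have a complication.* Low: (0.20 − 0.03)/0.95 = 17.9%. Standard: (0.30 − 0.09)/0.85 = 24.7%. The difference shrinks from 10.0 to 6.8 points, and the risk ratio moves from 0.67 to 0.72.
- *Same true risks; 10% removed in each arm; 50% of removed patients have a complication.* Low: (0.20 − 0.05)/0.90 = 16.7%. Standard: (0.30 − 0.05)/0.90 = 27.8%. The difference grows to 11.1 points.
- *No true effect, 20% in both arms; removal only among patients with a complication, 30% of them in the standard arm and 10% in the low arm.* Standard: 0.20 × 0.70/(1 − 0.06) = 14.9%. Low: 0.20 × 0.90/(1 − 0.02) = 18.4%. The observed risk ratio (low/standard) is 1.23 when the truth is 1.00.

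The bias can go in either direction, depending on inputs that the documents do not give.

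**The case against.** The case on the other side is substantial.

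- **The opening for removal is narrow.** The rule is discretionary. Patients in hospital are visited by staff, so failing to attend mostly means an unanswered call. That is a loss with or without the rule, and ending participation after a failed POD 90 call loses nothing more. This stands in part. If the calls count as study visits, a patient who misses the POD 30 call could be removed before survival at POD 90 is sought. Non-cooperation can also arise on the ward.
- **The causal link is an inference.** No section says that a patient with a neurologic deficit would be classed as uncooperative. The case of slurred speech and seizures in the Discussion followed a nephrectomy outside this trial. Patients with communication or compliance problems are excluded at entry, and follow-up staff are blinded to group. This stands against any claim that removal will follow embolism or differ by arm. Blinding limits selection by arm, but it does not prevent loss related to outcome.
- **The assumed losses are high.** Removing 5% and 15% averages 10%, so this one rule would use the whole drop-out allowance. This stands, and the figures show only what could happen.
- **A condensed article may leave follow-up after discontinuation to the full protocol.** This does not dispose of the point. The article states a conduct rule and says which data are kept, and the rule as stated conflicts with its ITT sentence.

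A reader might infer that the rule undermines ITT for every outcome, including the primary. The documents do not support that, because embolism grading is finished before any postoperative visit and is retained. Replacement of patients could remove a primary outcome, and conversions to open surgery are also excluded in the same section. Those are separate and larger issues.

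**Conclusion.** The point holds for the late secondary outcomes only. As written, ending participation and keeping only earlier data cannot be reconciled with analysing all randomised patients for 30-day complications, hospital-free days at day 28, ICU readmission after removal, and 90-day survival. The loss is avoidable, may be outcome-related, and falls outside the stated sensitivity analysis.

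Its size cannot be fixed from the documents. With one removal per arm the effect on the risk ratio is small. If the whole 10% allowance were used, the data would leave the risk ratio very uncertain. Both statements rest on the assumed 20% risk. No mortality figures are given, so informative censoring of survival is a possibility and not a finding. It would also go too far to conclude that patients harmed by embolism will be removed, or that the comparison will be biased towards one arm. The change is worth making because it is cheap and can only be made before the data are lost, but the concern is of moderate weight.

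**What to change.** Replace the investigator-removal sentence in Study dropouts with a rule to this effect: non-attendance or lack of cooperation ends only the assessment concerned. The patient stays in the trial. Length of stay, ICU use, 30-day complications and survival to day 90 are still collected from records and from the planned POD 30 and POD 90 calls, unless the patient withdraws consent to further data collection.

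This is a small wording change. It adds no visits and leaves clinical care unchanged. The cost is a few more contact attempts. Extending the sensitivity analysis alone would not be a substitute, because imputation cannot restore outcomes that could have been collected.

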### Statistical analysis

#### Sample size

The incidence of severe gas embolism in the right ventricular system detected by TEE will be used as the primary outcome parameter. Based on results from preliminary trial, the incidence of grade 3 and above gas embolism in LLR using low and standard intra-abdominal pressure was 45% and 69%, respectively. Sample size was calculated by a web-based calculator (http://powerandsamplesize.com/Calculators/). For the power of 80% and a level of significance of 5% against the two-sided alternative hypothesis, 126 participants are required to detect the observed difference in gas embolism incidence using chi-square test. Expecting 10% drop-out of participants, a sample size of 140 is required.

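### The dropout rules (exclusion at conversion to open surgery, replacement of some removed patients) contradict the promised intention-to-treat analysis, chiefly for outcomes after conversion

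*Protocol article*

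**What the plan says.** Four statements in the protocol article bear on who is analysed.

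- **Analysis:** "The intention-to-treat (ITT, all randomly assigned cases) population is used for all outcomes analysis". A supportive set is defined as well: "The supportive analysis is based on a full analysis set (FAS, all randomly assigned patients who received corresponding PP until liver resection". Multiple imputation and estimating-equation methods are planned as a sensitivity analysis "if more than 1% of missing data are found for the primary outcome".
- **Study dropouts, conversion to open surgery:** "These patients will be excluded from the study, and patient data until this moment will be included in the analysis".
- **Study dropouts, removal by the investigator:** participation "can also be ended by the investigator if the patient is uncooperative and/or does not attend the study visits". For these patients, "if too many data are missing (e.g., missing baseline, study visits, and other measurements included in the primary outcome"), then "the patient will be replaced by a new patient".
- **Sample size:** "Expecting 10% drop-out of participants, a sample size of 140 is required".

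Under Outcomes, the primary endpoint (gas embolism of grade 3 or higher) is observed by TEE for the whole of the laparoscopic resection. The secondary outcomes include complications within 30 days, hospital-free days at day 28 and 90-day survival.

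**The concern.** An ITT analysis of all outcomes needs every randomised patient to stay in the denominator and to be followed for those outcomes. Leaving the study at conversion prevents the second. For a replaced patient the first is left open.

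Conversion happens after randomisation and may plausibly depend on the assigned pressure, through working space or bleeding. A rule that ends follow-up at conversion therefore selects on something treatment may affect. The outcomes most exposed are those measured after surgery, where converted patients may well differ in prognosis from the rest.

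The primary outcome is exposed to a lesser degree. A converter with no severe embolism so far has been watched for less time than planned, and the protocol does not say how that patient is classified. Its Discussion holds that embolism risk probably rises with surgical duration and the size of the transection, so a shorter window can miss events.

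**Working it through.** **1. The sections side by side**

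| Patient | Analysis section | Study dropouts section | Consistent? |
|---|---|---|---|
| Converter, outcomes after conversion | ITT, all outcomes | Out of the study; earlier data only | No |
| Converter, severe embolism before conversion | ITT | Earlier data analysed, so the event counts | Yes |
| Converter, no event before conversion | ITT | Earlier data analysed; classification not stated | Unclear |
| Removed by the investigator, too much missing | ITT | Replaced; ITT status not stated, no threshold | Unclear |

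The supportive set does not repair this. It requires the assigned pressure up to resection, which is itself a condition met after randomisation.

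**2. The plan's own sample size**

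Inputs from Sample size: 45% v 69%, 80% power, two-sided 5%.

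n per arm = (1.960 + 0.842)² × [0.45×0.55 + 0.69×0.31] / 0.24² = 7.849 × 0.4614 / 0.0576 = 62.9, so 63 per arm and 126 in all. Then 126 / 0.90 = 140. Both figures reproduce. The 140 already allows for 14 non-evaluable patients, so replacement is not needed to reach 126.

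**3. The missing-data trigger**

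1/140 = 0.7% and 2/140 = 1.4%, so two missing primary outcomes set off the sensitivity analysis. A replaced patient contributes to that count only if still in the ITT set.

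**4. Possible effect on the primary outcome (illustration only)**

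Assumptions, none of them from the protocol: true incidence p = 60% in both arms (no effect), 70 per arm, conversion c = 15% in the low-pressure arm and 5% in the standard arm, and a fraction m of converters' events falling after conversion, unseen and counted as non-events.

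Observed incidence = p × (1 − c × m). The one-sided false-positive rate is the exact sum, over all pairs of binomial counts at 70 per arm, of the probability that the Pearson chi-square test is significant at two-sided 5% in favour of low pressure.

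| Events missed (m) | Low pressure | Standard | RR | False-positive rate favouring low pressure |
|---|---|---|---|---|
| None | 60.0% | 60.0% | 1.00 | 2.4% |
| Half | 0.60×(1−0.075) = 55.5% | 0.60×(1−0.025) = 58.5% | 0.95 | 5.4% |
| All | 0.60×(1−0.15) = 51.0% | 0.60×(1−0.05) = 57.0% | 0.89 | 10.7% |

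Other assumed rates:

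- 10% v 3%: 4.3% (half missed) and 7.2% (all missed).
- 20% v 5%: 7.7% and 18.9%.
- 5% v 5%: RR 1.00 and no bias under the null.
- 15% v 5% with the arms exchanged: the bias reverses and works against low pressure.

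If low pressure truly works (45% v 69%), equal conversion costs power instead. At 5% in each arm with all of converters' events missed, the difference shrinks from 24.0 to 22.8 points and power at 70 per arm from 82.5% to 77.9%.

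**The case against.** The strongest reply is that the primary comparison is largely intact, and much of that reply stands.

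- **Converters are not dropped from the primary outcome.** Their TEE data up to conversion are analysed. An embolism that prompted conversion would come before it and be recorded.
- **The short window has a defence.** The endpoint is defined over the laparoscopic resection, and the laparoscopic phase ends at conversion. Stopping observation there can be read as part of the estimand.
- **Classification of event-free converters is not stated.** A reader might infer that they are counted as non-events. No section says so. They might instead be treated as missing and imputed, and such detail may sit in an analysis plan that is not shown.
- **Replacement is narrow.** A reader might take it to cover anyone with missing data. It covers only patients whose participation the investigator ends, and then only when too much is missing. Because the primary outcome is recorded in theatre, a patient who later misses visits usually already has it. Nothing says that a replaced patient's data are deleted.
- **The illustration rests on assumed unequal conversion.** Deep neuromuscular blockade in both arms, a single surgeon, the BMI limit and the exclusion of abdominal cancer with adhesion may all keep conversions few.

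None of this reconciles leaving the study at conversion with ITT for outcomes measured afterwards. Nor does it supply the missing threshold or the ITT status of replaced patients.

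**Conclusion.** The contradiction is in the text and should be resolved. It is firm for outcomes after conversion: as written, 30-day complications, hospital-free days and 90-day survival omit converters, so they are not ITT. The replacement rule is ambiguous and, given the 10% allowance, unnecessary.

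For the primary outcome the point is a risk of unknown size. A reader might conclude that the primary comparison has lost the protection of randomisation. The documents do not support that, because events before conversion count and the protocol gives no conversion rates. The rates of 5.4% and 10.7% hold only under the stated 15% v 5% conversion and the stated share of missed events; the second is an upper bound for that scenario. Equal conversion leaves the null unbiased.

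**What to change.** Amend Study dropouts as follows.

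1. Every randomised patient, including converters and those removed by the investigator, stays in the ITT set as randomised and is followed to day 90 unless consent is withdrawn.
2. Delete the replacement rule. Failing that, state that replaced patients remain in ITT and count towards the 1% missing-data trigger, and define how much missing data is too much.
3. Keep the use of TEE data up to conversion for the primary outcome, and state how a converter without an event is classified.
4. Report conversions by arm, and add one pre-specified sensitivity analysis for event-free converters: either conversion counted as an event, or imputation of the unobserved remainder.

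The cost is amendment wording, a little extra analysis and a few more telephone contacts at days 30 and 90, which are already in the visit plan. Without replacement, the evaluable number may fall towards the planned 126. At 45% v 69% the pooled test then has 78.4% power with 63 per arm, against 82.5% with 70. The clinical handling of conversion is not in question.
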